## Abstract

**Introduction:**

Methamphetamine (MA) use disorder is an important public health concern. MA withdrawal is often the first step in ceasing or reducing use. There are no evidence-based withdrawal treatments, and no medication is approved for the treatment of MA withdrawal. Lisdexamfetamine (LDX) dimesilate, used in the treatment of attention deficit hyperactivity disorder and binge eating disorder has the potential as an agonist therapy to ameliorate withdrawal symptoms, and improve outcomes for patients.

**Methods:**

A single arm, open-label pilot study to test the safety and feasibility of LDX for the treatment of MA withdrawal. Participants will be inpatients in a drug and alcohol withdrawal unit, and will receive a tapering dose of LDX over five days: 250mg LDX on Day 1, reducing by 50mg per day to 50mg on Day 5. Optional inpatient Days 6 and 7 will allow for participants to transition to ongoing treatment. Participants will be followed-up on Days 14, 21 and 28. All participants will also receive standard inpatient withdrawal care. The primary outcomes are safety (measured by adverse events, changes in vital signs, changes in suicidality and psychosis) and feasibility (the time taken to enrol the sample, proportion of screen / pre-screen failures). Secondary outcomes are acceptability (treatment satisfaction questionnaire, medication adherence, concomitant medications, qualitative interviews), retention to protocol (proportion retained to primary and secondary endpoints), changes in withdrawal symptoms (Amphetamine Withdrawal Questionnaire) and craving for MA (visual analogue scale), and sleep outcomes (continuous actigraphy and daily sleep diary).

**Discussion:**

This is the first study to assess lisdexamfetamine for the treatment of acute MA withdrawal. If safe and feasible results will go to informing the development of multi-centre randomised controlled trials to determine the efficacy of the intervention.

## Introduction

An estimated 29 million people, or 0.7% of the world’s population aged between 15–64 years old, consumed amphetamine or methamphetamine (MA) in 2017 (hereafter referred to collectively as MA to reflect the most recent data on the context of the Australian market [1, 2]). The use of MA has been associated with depression and anxiety, psychosis, suicidal behaviour, cardiovascular, respiratory and dermatological conditions, blood borne virus transmission, non-fatal injury as well as overdose and death [3–6]. The global, age-standardised rate of MA/amphetamine dependence is estimated to be 96 people per 100,000 [7].

Cessation of MA use following frequent and prolonged use can result in a characteristic withdrawal syndrome, which emerges within hours to days after ceasing or reducing use [8]. This acute withdrawal syndrome is reported to last around 7–10 days and has been characterised by dysphoria, fatigue, sleep disturbances, vivid dreams, increased appetite, and psychomotor agitation or retardation, with symptoms peaking within the first 7 days [8–11]. Successful withdrawal can facilitate engagement with, and a transition to, ongoing treatment (e.g. residential rehabilitation, counselling), resulting in improved health and welfare [12, 13], and early abstinence of at least two weeks is a predictor of longer-term treatment success [14].

There are no evidence-based pharmacotherapies for the treatment of MA withdrawal [10]. Standard care generally involves management of MA withdrawal symptoms (e.g., benzodiazepines to manage anxiety and agitation) despite limited evidence of effectiveness in improving withdrawal outcomes [15]. Neurobiological models of MA withdrawal suggest that acute withdrawal symptoms (e.g. intense cravings, irritability and poor concentration) may result from dopaminergic dysfunction related to chronic exposure to high dose amphetamines [16, 17]. These changes have been correlated with mood and behavioural disturbances seen in people with chronic MA use [18]. At least partial recovery in dopamine transporter function occurs over time, however, this can take months [19]. In contrast, rodent models show the neurobiological changes that occur in withdrawal are potentially immediately reversible with administration of a stimulant [20]. Agonist therapies have been effective in the treatment of withdrawal for other substances (for example buprenorphine for opioid withdrawal [21]), and agonist-like therapies for MA dependence have shown promise in the past, particularly in their effects on craving [22].

A potential candidate drug to treat MA withdrawal is lisdexamfetamine. Lisdexamfetamine (LDX) is a pharmacologically inactive pro-drug of dexamphetamine, a central nervous stimulant which increases extracellular dopamine [23]. LDX has regulatory approval in Australia for the indications for Attention-Deficit / Hyperactivity Disorder (ADHD) and Binge Eating Disorder at doses up to 70 mg per day [24]. LDX is absorbed after oral administration and hydrolysed to inactive metabolites and active dexamphetamine by red blood cells [25]. This results in a slower onset of action/effect and lower peak dopamine concentration compared with immediate release dexamphetamine [26, 27], enabling once daily dosing.

LDX doses of up to 250mg per day have been found to be safe and tolerable in both stimulant-naïve people and a pilot study of people who use MA [23, 28, 29]. A tapering dose regimen is proposed in this protocol to allow for maximum potential attenuation of early withdrawal by providing reducing stimulant exposure through the first five days, when withdrawal symptoms are at their most severe and ensure no residual withdrawal from LDX upon ceasing treatment due to the tapering dose. As the ineffective treatment of MA withdrawal symptoms may lead to higher rates of relapse to use [30, 31], the ability for LDX as a prodrug of dexamphetamine to ameliorate withdrawal symptoms and craving for MA has the potential to improve treatment outcomes during acute withdrawal [32].

This report is a protocol for an open-label, single-arm pilot clinical trial. The protocol was developed in conjunction with SPIRIT guidelines and adheres to the Australian National Statement on Ethical Conduct in Human Research, and Good Clinical Practice guidelines [33–35].

### Objectives

This study aims to assess a five-day tapering-dose regimen of LDX for the management of acute MA withdrawal in an inpatient withdrawal setting. We hypothesise that a tapering dose of LDX will be safe and feasible to deliver during inpatient withdrawal from MA.

The primary objective is to determine the safety and feasibility of a 250mg tapering dose of LDX over five days of inpatient treatment. Secondary objectives are: (i) to describe the acceptability of the treatment regimen to participants; (ii) to describe participant retention to the protocol; (iii) to describe changes in withdrawal severity, and (iv) MA craving during and after the treatment regimen; and (v) to describe the sleep wake cycle of people with acute MA withdrawal receiving a five-day tapering dose of LDX.

## Materials and methods

### Trial design

This study is an open-label, single-arm, pilot clinical trial of a five-day tapering dose regimen of LDX for acute MA withdrawal. Participants are admitted to an inpatient withdrawal unit for up to seven days (five days of medication and two additional optional days for transition to ongoing treatment [e.g. residential rehabilitation, counselling]) and are followed up via telephone or in person once a week until Day 28 (three weeks post discharge).

### Sample size

As this is a pilot study, it is not powered to detect differences in treatment efficacy. This study will therefore seek to enrol 15 participants, conventional for studies of this nature [36, 37]. Findings will inform planning for a large-scale RCT of LDX for treatment of MA withdrawal.

### Study setting

This study is conducted at a single site inpatient alcohol and other drug withdrawal unit in Sydney, New South Wales, Australia.

### Eligibility criteria

Inclusion criteria are adults over the age of 18 years who: are presenting to inpatient drug treatment services seeking treatment for MA withdrawal; have methamphetamine use disorder (MAUD) as determined by an Addiction Medicine specialist according to the Diagnostic and Statistical Manual of Mental Disorders, 5th Edition (DSM-5) Criteria [11]; report last use of MA within 72 hours of the planned first study drug dose; have a positive urine drug screen for MA on admission, and; are willing and able to provide written informed consent and comply with the study protocol.

Exclusion criteria are: participants who are lactating, pregnant or of childbearing potential and not willing to avoid becoming pregnant during the study; expected concurrent withdrawal from alcohol, opioids, benzodiazepines, gamma-hydroxybutyrate or other gabapentinoids; known contraindications to LDX (as per the product label [24]); a medical or psychiatric comorbidity which in the opinion of a study medical officer renders a patient unsuitable for the study; or, involuntary patients. Full criteria are described in Table 1.

**Table 1 pone.0275371.t001:** Eligibility criteria.

Inclusion Criteria	Exclusion Criteria
Adult over the age of 18 years Presenting to inpatient drug treatment services seeking treatment for acute MA withdrawal (e.g. self-presenting to the centralised intake line, presented to the Emergency Department, presented to the Alcohol and Drug Service etc.) Methamphetamine Use Disorder as determined by an addiction medicine specialist according to the Diagnostic and Statistical Manual of Mental Disorders, 5^th^ Edition (DSM-5) criteria Last MA use within 72 hours of planned first dose of investigational product Positive urine drug screen for methamphetamines Willing and able to provide written informed consent and willing to participate in and comply with the study protocol	Women who are: lactating; pregnant; or are of childbearing potential and not willing to avoid becoming pregnant during the study Expected concurrent withdrawal from alcohol, opioids, benzodiazepines, gamma-hydroxybutyrate or other gabapentinoids Known contradiction(s) to lisdexamfetamine (as per product information [24]) including: Advanced arteriosclerosis Symptomatic cardiovascular disease including cardiac arrhythmia, ischaemic heart disease Moderate to severe hypertension Hyperthyroidism Known hypersensitivity or idiosyncratic reaction to sympathomimetic amines or any of the excipients Glaucoma Agitated states such as severe anxiety, tension and agitation During or within 14 days following the administration of monoamine oxidase inhibitors (hypertensive crises may result) Pheochromocytoma Tics, Tourette’s syndrome Patients who currently exhibit severe depression, anorexia nervosa, psychotic symptoms or suicidal tendency Significant medical or psychiatric condition which, in the opinion of a study medical officer, renders a patient unsuitable for the study Involuntary patient status

Potential participants are pre-screened by telephone or in person by a researcher prior to admission. This process facilitates orientation to the study, gauges interest, and assesses potential eligibility to participate. Individuals considered potentially eligible are invited to a formal eligibility assessment by a specialist in Addiction Medicine. The assessment schedule, including eligibility assessments, is outlined in Fig 1.

**Fig 1 pone.0275371.g001:**
[figure not shown]
Schedule of enrolment, interventions, and assessments.

### Intervention

Participants receive a tapering dose of oral lisdexamfetamine dimesilate in 50mg capsules, beginning with 250 mg once daily (OD) on Day 1, and reduced by 50 mg per day, to 50 mg OD on Day 5 (Table 2).

**Table 2 pone.0275371.t002:** Study drug dosing schedule.

Study day	Day 1	Day 2	Day 3	Day 4	Day 5	Day 6	Day 7
Lisdexamfetamine	250 mg OD^a^	200 mg OD	150 mg OD	100 mg OD	50 mg OD	-	-

^a^ OD, daily; dosing should be within +/- 1 hour of scheduled dosing time

LDX at a dose of 250 mg is equivalent to approximately 74 mg of dexamphetamine [38], and similar doses of sustained release dexamphetamine (60-110mg) have previously been demonstrated to decrease MA withdrawal severity and cravings, and increase retention in care [39, 40].

### Data collection

#### Outcomes

*Primary outcomes*. Safety is assessed by Adverse Events (AEs) and vital statistics recorded during each study visit. AEs will be analysed and reported for seriousness, severity, causality, relatedness, and expectedness [41]. Vital signs (heart rate, blood pressure, temperature, oxygen saturation and respiratory rate) are recorded four times daily during the inpatient period. Safety is further assessed through differences in symptoms of psychosis and hostility obtained using the psychosis and hostility items of the Brief Psychiatric Rating Scale (BPRS) [42, 43], and suicidality measured by the Columbia Suicide Severity Rating Scale (C-SSRS) at Days 1 and 5 [44]. Feasibility is measured through the proportion of screen and pre-screen failures and time taken to enrol sample.

*Secondary outcomes*. Medication acceptability is measured by the Treatment Satisfaction Questionnaire for Medications II (TSQM-II) [45], medication adherence (proportion of prescribed doses taken and reasons for missing doses), proportion and type of adjuvant symptomatic medication required, and qualitative interviews. Retention is assessed by the proportion of participants retained in the study until Days 5, 7, 14, 21 and 28. Changes in subjective withdrawal severity are measured at each time point using the Amphetamine Withdrawal Questionnaire (AWQ) [46] through to Day 28. Changes in craving for MA during the inpatient period are assessed using a 100mm Visual Analogue Scale (VAS) [47]. Participant sleep is objectively monitored through continuous actigraphy (Philips Actiwatch 2^®^) and subjective sleep quality is measured with a modified Consensus Sleep Diary (CSD) [48].

To describe the sample additional baseline assessments include: the Wender-Utah rating scale (WURS), to screen for co-existing ADHD [49]; and severity of dependence assessed with the Severity of Dependence Scale (SDS) [50]. Quality of life and level of social support is measured using the Personal Wellbeing Index (PWI) and ENRICHD Social Support Inventory (ESSI), respectively [51, 52].

### Procedure

#### Day 0 (screening and eligibility)

When a potential participant is admitted to the inpatient withdrawal management unit, a researcher provides an overview of the study, reviews the participant information sheet with the patient, and answers questions as needed. Patients who are interested in participating in the study are asked to provide written informed consent. The day of admission is defined as Day 0 of the study, and after informed consent is provided participants are screened for eligibility by an addiction medicine specialist signed on to the study as an investigator. If eligible, participants are formally enrolled in the trial and a medical screening and assessment is undertaken. Baseline data including confirmation of recent MA use through a urine drug screen is collected. Usual inpatient withdrawal care (including symptomatic management and psychosocial support) is provided. Concomitant psychosocial therapy and AEs are recorded. Protocolised adjuvant symptomatic treatment (diazepam for anxiety (maximum 10mg four times daily [QID]) and olanzapine for psychosis (maximum 5mg three times daily [TDS])), as per standard of care are available alongside the experimental treatment as per standard of care in accordance with the protocol.

#### Days 1–5 (inpatient period, active medication)

Day 1 is defined as the first morning of admission, to allow for consistent morning dosing for LDX. Participants are assessed daily for safety, AEs, concomitant medication, and concomitant psychosocial therapies. Daily measures of treatment satisfaction, withdrawal severity, cravings for MA, and quality and duration of sleep are assessed.

Participants are invited to participate in a qualitative interview to examine their experiences of participating in the clinical trial to ensure any subsequent trials will include participant perspectives. Interviews are one-on-one, semi-structured, and approximately 30 minutes in duration. They are conducted by study staff trained in qualitative interviewing. One interview will take place between Days 3 and 7. Interviews are conducted in a private room, and electronically recorded and transcribed.

#### Days 6–7 (inpatient period, no medication)

Days 6–7 are optional for ongoing inpatient care and monitoring. Adjuvant medication, wraparound withdrawal services and discharge planning continue to be offered as usual. Participants will be assessed daily for AEs, concomitant medications, and concomitant psychosocial therapies.

Admission may extend beyond Day 7 if clinically indicated, independent of the study.

LDX is not available after Day 5. Ongoing standard treatment is individualised in collaboration with external treating clinicians (i.e., outpatient stimulant treatment programs, residential rehabilitation, etc.). Treatment access and engagement following the inpatient withdrawal period is recorded through to Day 28.

#### Days 14, 21 and 28 (follow-up)

Participants receive telephone and short message service (SMS) follow-up from a researcher on Days 14, 21 and 28. Safety, concomitant medication and psychosocial therapy, questionnaire completion and ongoing care will be recorded.

All AEs will be followed-up to resolution or until Day 28, whichever is the shorter, regardless of relatedness to study drug.

Participants are reimbursed with supermarket vouchers in line with standard practice [53], at Baseline ($20) and Days 5 ($30), 7($30) 14 ($30), 21 ($30) and 28 ($30) [53]. Total possible remuneration is $170.

#### Participant study discontinuation

Participants who wish to discontinue protocol treatment are offered the opportunity to continue to participate in all remaining research assessments. For those participants who revoke their consent to participate in the study, no further data are collected.

#### Study withdrawal criteria

Consistent with the safety protocols that are standard care at the enrolling site, review by an Addiction Medicine specialist (signed onto the study protocol) will occur where a participant records a single episode of systolic blood pressure >180mmHg or <100mmHg, a resting heart rate >120 beats per minute (bpm) or <50 bpm, or requires >40mg of diazepam over a 24-hour period to manage symptoms. These events are considered AEs. Any AE that is determined to be potentially treatment related and considered a risk to participant safety by a study doctor will result in withdrawal of the participant from the trial for safety concerns.

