### Statistical methods

The adverse event verbatim descriptions will be classified into standardized medical terminology using the Medical Dictionary for Regulatory Activities (MedDRA) version 19.1. AEs will be coded to primary System Organ Class (SOC) and preferred term (PT) using MedDRA. Descriptive statistics will be used to analyse all AEs by causality and relatedness. Changes in vital signs will be described using medians and interquartile ranges. The proportion of screen failures and participants who commenced study drug; proportion who achieve each dose; and, proportion who are retained in the study or revoke consent will be analysed. Secondary outcomes measure: changes in medication tolerability; proportion of participants who reached primary and secondary end points; MA withdrawal and craving severity; and, quality and duration of sleep. These will be tested for statistical significance using Wilcoxon rank-sum test for non-parametric data. All tests of significance will be conducted at a two-sided alpha level of 0.05. As this is an exploratory study we will: (i) conduct analyses of observed data only; (ii) conduct sensitivity analyses which account for missing data by imputation; and, (iii) report missing data and limitations.

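### A participant with a risky, possibly treatment-related AE is withdrawn from the trial rather than from LDX, so the Day 5 psychiatric safety scores may be missing for those harmed

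*Protocol article*

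**What the plan says.** All references are to the protocol article.

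- **Study withdrawal criteria.** Out-of-range systolic blood pressure or heart rate, or more than 40 mg of diazepam in 24 hours, triggers specialist review, and "These events are considered AEs". Separately, any AE judged possibly drug related and also "considered a risk to participant safety by a study doctor will result in withdrawal of the participant from the trial for safety concerns". Stopping LDX alone is not mentioned.
- **Participant study discontinuation.** "Participants who wish to discontinue protocol treatment are offered the opportunity to continue to participate in all remaining research assessments". The only stated end to data collection is revoked consent.
- **Abstract, Methods.** The primary safety outcome includes "changes in suicidality and psychosis".
- **Outcomes, Primary outcomes.** Safety includes "suicidality measured by the Columbia Suicide Severity Rating Scale (C-SSRS) at Days 1 and 5". The BPRS psychosis and hostility items stand in the same sentence, and the day phrase can be read as covering both scales.
- **Days 14, 21 and 28 (follow-up).** "All AEs will be followed-up to resolution or until Day 28, whichever is the shorter, regardless of relatedness to study drug".
- **Statistical methods.** The plan is to "conduct analyses of observed data only", with sensitivity analyses by an unnamed imputation method and a report of missing data and limitations.

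**The concern.** The protocol separates stopping the drug from leaving the study, but applies that distinction only to participants who choose to stop. Someone who stops by preference is offered every remaining assessment. Someone stopped by a study doctor because the drug may be harming them is, on the wording, out of the trial.

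That matters for a scale outcome defined as a Day 1 to Day 5 change. People with current psychotic symptoms or suicidal tendency are excluded at entry, so deterioration would appear mainly as new cases during dosing. Those are the cases the withdrawal rule may remove before Day 5. The observed change would then describe the participants who tolerated treatment and could look better than the experience of everyone dosed. The result is meant to inform a planned randomised trial.

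Retention is affected too. It is defined by "Retention is assessed by the proportion of participants retained in the study until Days 5, 7, 14, 21 and 28", so a doctor-ordered stop counts as a loss to the study even if the participant would have stayed for assessments.

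**Working it through.** The protocol gives no figure on this point to reproduce: the sample of 15 is set by convention, no withdrawal rate is stated, and no threshold for worsening is defined. The point rests on the text; the arithmetic only illustrates its size.

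**Step 1. The rules side by side**

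| Situation | What the article states | Day 5 C-SSRS/BPRS provided for? |
|---|---|---|
| Participant wishes to stop LDX | Offered all remaining assessments | Yes |
| Participant revokes consent | No further data | No, properly |
| Study doctor judges AE potentially related and a risk | Withdrawn from the trial | Not stated |

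AE follow-up to Day 28 covers the third row for the event itself, but that text names neither scale. The daily safety assessment described for Days 1–5 names neither scale either.

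**Step 2. Assessment days at stake**

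Fixed assessment days: Days 1 to 5 (5) plus Days 14, 21 and 28 (3), so 8. Optional Days 6 and 7 are not counted. If withdrawal ends participation after the Day d assessment, days lost = (5 − d) + 3:

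- d = 1: 4 + 3 = 7
- d = 2: 3 + 3 = 6
- d = 3: 2 + 3 = 5
- d = 4: 1 + 3 = 4

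Day 5 is lost in every case.

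**Step 3. Effect on the observed Day 5 result**

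Assume w of 15 worsen and are withdrawn before Day 5, and nobody else worsens. Observed = 0/(15 − w); all dosed = w/15. Intervals are Clopper-Pearson 95%; for a zero count the upper limit is 1 − 0.025^(1/n), for example 1 − 0.025^(1/14) = 23.2%.

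| w | Observed at Day 5 | 95% interval | All dosed | 95% interval |
|---|---|---|---|---|
| 1 | 0/14 = 0% | 0 to 23.2% | 1/15 = 6.7% | 0.2 to 31.9% |
| 2 | 0/13 = 0% | 0 to 24.7% | 2/15 = 13.3% | 1.7 to 40.5% |
| 3 | 0/12 = 0% | 0 to 26.5% | 3/15 = 20.0% | 4.3 to 48.1% |

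The intervals overlap throughout. The issue is who is left out, not a difference that 15 participants could detect.

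**Step 4. Whether the rule is likely to be used**

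For an assumed per-participant risk p of a safety withdrawal before Day 5, the chance of at least one in 15 is 1 − (1 − p)^15:

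- p = 5%: 53.7%
- p = 10%: 79.4%
- p = 20%: 96.5%

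These risks are assumptions and cover safety withdrawals of any kind, not only psychiatric ones.

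**The case against.** The strongest reply is that the article can be read the other way. Following every AE to resolution or Day 28 is hard to do if safety withdrawal ends all contact, and data collection is said to stop only when consent is revoked. Leaving the trial may therefore be loose wording for leaving treatment. The schedule figure is not shown, and the full protocol may settle both the BPRS timing and what is done at an early stop. This stands as a reason for caution: the text is unsettled, and loss of data is possible rather than certain. It does not remove the point, because the article states a rule and staff following its words would have no instruction to collect the Day 5 scales.

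Second, the harm is not hidden. AEs are themselves a primary safety component, the DSMB reviews accumulating safety data, and the dose-achieved and retention proportions would show the withdrawals. This stands, and it confines the defect to the scale-based component.

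Third, the plan includes imputation in sensitivity analyses and will report missing data. That softens the problem. But imputation would draw on participants who stayed, and cannot recover scores missing because of harm.

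Fourth, the psychiatric route is narrow. The named review triggers are cardiovascular signs and diazepam dose, olanzapine is available for psychosis alongside LDX, and withdrawal needs a doctor's judgement of both relatedness and risk. This is correct and limits how often the outcome-linked case would arise. Once that judgement is made, however, the rule leaves no alternative to trial withdrawal.

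**Conclusion.** The concern holds. As written, the safety withdrawal rule removes the participant from the trial, and nothing in the article keeps the Day 5 C-SSRS or BPRS for that person. The C-SSRS part is firm on timing. The BPRS part depends on reading the Days 1 and 5 phrase as covering both scales.

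The size is modest in absolute terms, but the loss is tied to the outcome: under the illustration, one to three missing participants turn 6.7% to 20.0% worsened into an observed 0%. This assumes that everyone who worsens is withdrawn before Day 5 and that nobody else worsens. AE reporting is unaffected. The point should be corrected, but it does not undermine the trial's safety reporting as a whole. Confidence is medium, because the wording may be looser than the intended practice.

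**What to change.** 1. In Study withdrawal criteria, make an AE of this kind stop LDX rather than trial participation.
2. In Participant study discontinuation, extend the offer of all remaining assessments, including Day 5 and Days 14, 21 and 28, to participants stopped by a study doctor, unless they revoke consent.
3. Take the C-SSRS and the BPRS psychosis and hostility items when LDX is stopped early.
4. Report the Day 1 to Day 5 scale change beside the number stopped for psychiatric AEs and the number with a Day 5 score. The planned dose, retention and missing-data reporting already supplies part of this.

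**Cost.** One sentence changes in each of the two sections. There is one extra short scale set per participant stopped early (1 to 3 sets in the illustration), and 4 to 7 assessment days are kept for each one who agrees. LDX still stops at once, so participant protection is unchanged. The downside is some added burden on people who have just had an AE, and some may decline.
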